#### Testing hypotheses 2a–2c

To test the moderation hypotheses, we will use linear regression analysis. Change in pain intensity will be the response (criterion) variable. Pre-treatment measures of pain catastrophizing, mindfulness, and behavioral activation will be entered in the model as possible moderators; terms representing the interaction between treatment condition and the moderators will test hypothesis 2a–2c. If the coefficient for a certain interaction is statistically different from zero, this will be interpreted as a moderation effect of the moderator present in the interaction.

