### Aims

This study will address two specific aims with corresponding hypotheses:
Aim 1: to determine the efficacy of group-based, videoconference-delivered MBCT and CBT interventions, relative to usual care, in reducing pain intensity (the primary outcome) in adults with chronic pain and MS;
Hypothesis 1 (primary study hypothesis): participants randomly assigned to MBCT or CBT will report significantly greater reductions in average pain intensity (primary outcome) relative to participants assigned to usual care at post-treatment (primary endpoint).Aim 2: to increase our ability to more effectively match patients to treatments by identifying pain treatment moderators. Although on average we expect similar outcomes in MBCT and CBT, we expect that there will be individual differences in who responds to each treatment. Specifically, we anticipate that pre-treatment levels of mindfulness, behavioral activation (activity), and pain catastrophizing will be associated with treatment response for the active treatment arms. Thus, to address Aim 2, we will explore pre-treatment levels of mindfulness, behavioral activation, and pain catastrophizing as predictors of response to MBCT and CBT;
Hypothesis 2a: pre-treatment pain catastrophizing will be positively associated with treatment response for the two active treatment arms, but not the control condition;Hypothesis 2b: pre-treatment behavioral activation will be positively associated with treatment response for the two active treatment arms, but not the control condition;Hypothesis 2c: pre-treatment mindfulness will be positively associated with treatment response to MBCT but not to either CBT or the control condition.

In addition to testing these specific hypotheses, we will use study data to address the following exploratory aims:
The effects of MBCT and CBT relative to each other on both the primary (i.e., average pain intensity) and secondary outcomes (pain interference and key co-morbid symptoms including fatigue, sleep, and depressive symptoms), as hypothesis 1 pertains only to the effects of CBT and MBCT relative to the control, not to each other;The relative effects of all three treatment conditions on the secondary outcomes;The maintenance, loss or gain in any treatment effects at 6 months post-treatment;Dose effects; andAdditional potential moderators of outcome, including demographics, baseline pain characteristics (e.g., pain severity, pain type) and baseline depressive symptom severity and fatigue.

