### Participant eligibility, recruitment, and consent procedures

Inclusion criteria are (1) 18 years of age or older; (2) a diagnosis of clinically definite MS confirmed by participant’s provider; (3) the presence of chronic pain, defined as average pain intensity in the past week of at least moderate severity (defined as ≥ 3 on the 0–10 numerical rating scale (NRS)) [15] and pain of at least 3 months duration, with pain reportedly present on at least half the days in the past 3 months; (4) reads and speaks English; (5) has access to and is able to communicate over the telephone; and (6) has a computer or digital device with video capabilities (any operating system) with Internet access. Exclusion criteria are (1) severe cognitive impairment defined as ≥ 2 errors on the 6-item Cognitive Screener [16]; (2) currently in psychotherapy or counseling for pain more than once a month; and (3) previously participated in a pain study that used CBT or MBCT.

Participants will be primarily recruited through advertisements on national websites, including the National MS Society’s website and ClinicalTrials.gov, as well as through national consumer publications (e.g., Momentum, the National MS Society’s magazine). At the UW MS Center, providers may directly refer patients to the study. Individuals may also self-refer to the study upon viewing a study brochure or flyer posted in the UW MS Center or in the community. If necessary to reach the required sample size, we will also recruit via targeted mailings to individuals in our UW MS research registry of > 1400 adults with MS from across the USA.

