### Randomization, allocation concealment, and procedures to minimize bias

Enrolled participants who complete the pre-treatment assessment will be randomly assigned to one of the three conditions. The trial manager is not involved in any outcome assessments and therefore will carry out randomization following the protocol designed by the study biostatistician ([name]) prior to the study’s start. Participants will be randomized in stratified blocks using a computer-generated, password-protected randomization list, with randomization stratified by sex and pre-treatment pain intensity (mild/moderate or severe) to control for variation in outcome attributable to each stratification variable. The trial manager will notify participants of their allocation. All staff involved in data collection and management will be kept unaware of the participants’ group assignments and will explicitly inform participants that they (staff) are to remain blinded during the course of the study. The biostatistician will also be unaware of treatment assignment. Participants will be informed that the CBT and MBCT are each a type of pain self-management intervention and that the study’s purpose is to determine which treatment is more beneficial. Thus, only the staff involved in data collection and management are blinded, whereas study participants and the trial manager will have access to group allocation. We do not anticipate any requirement for unblinding during the course of the trial.

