#### Moderator domains

The primary moderator variables will be catastrophizing, mindfulness, and behavioral activation (Table 1). Exploratory moderators include demographic variables (sex, age), pain characteristics (pre-treatment pain intensity, pain type (neuropathic versus non-neuropathic pain)), baseline cognitive functioning, treatment expectancies, and baseline levels of the study outcomes and co-morbid symptoms (depressive symptoms, fatigue, and sleep disturbance).

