We will use an intent-to-treat approach to test hypothesis 1: all randomized participants will be included based upon their assigned treatment group regardless of actual treatment received and adherence. Hypothesis 1 states that participants randomly assigned to MBCT or CBT will report significantly greater reductions in average pain intensity relative to participants assigned to usual care, post-treatment (primary endpoint). This will be tested using analysis of covariance, with treatment condition (MBCT, CBT, usual care) as the explanatory variable, the pre-treatment average pain intensity score as the covariate, and change from pre-treatment to post-treatment score in average pain intensity as the response variable. Support for hypothesis 1 would emerge if after controlling for the pre-treatment pain score, there are differences in the response variable by intervention group, and subsequent post-hoc analyses comparing the adjusted means indicate greater reductions in pain intensity in the MBCT and CBT conditions, relative to the usual care condition. Although we anticipate that MBCT and CBT will have similar effects on the primary outcome variable, these analyses will also allow us to compare, as an exploratory test, the relative effects of MBCT and CBT. Effect sizes will be computed and reported. Secondary outcomes will be assessed using similar analyses to those used to test hypothesis 1.

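### The moderator regression for hypotheses 2a–2c leaves out pre-treatment pain: its interaction tests stay free of regression-to-the-mean bias but lose precision, and a moderator effect may partly be a baseline-pain effect

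*Protocol article*

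**What the plan says.** The subsection Testing hypotheses 2a–2c describes a linear regression. "Change in pain intensity will be the response (criterion) variable". The terms follow: "Pre-treatment measures of pain catastrophizing, mindfulness, and behavioral activation will be entered in the model as possible moderators", and "terms representing the interaction between treatment condition and the moderators will test hypothesis 2a–2c". An interaction coefficient that differs significantly from zero is to be read as moderation by the variable in that interaction.

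Pre-treatment pain is not named there. Elsewhere it is treated as important:

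- The hypothesis 1 analysis of covariance, for the same change score, has "the pre-treatment average pain intensity score as the covariate".
- The randomization section describes assignment "with randomization stratified by sex and pre-treatment pain intensity (mild/moderate or severe"), with the stated purpose of controlling outcome variation due to those factors.
- Moderator domains lists it among the exploratory moderators: "pain characteristics (pre-treatment pain intensity, pain type (neuropathic versus non-neuropathic pain")).

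The Aims word hypothesis 2a so that it covers the control arm: "pre-treatment pain catastrophizing will be positively associated with treatment response for the two active treatment arms, but not the control condition". Hypothesis 2b has the same form for behavioral activation.

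**The concern.** Two models for one change score treat its strongest likely predictor differently. Baseline pain is a covariate for Aim 1 and absent for Aim 2. Three consequences need checking.

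- **Precision.** Change is correlated with baseline. Leaving baseline out keeps explainable variation in the residual. The Statistical power section sizes the trial for hypothesis 1 only, so the interaction tests have no stated power to spare.
- **Attribution.** The protocol itself regards baseline pain as a possible moderator. If the treatment effect varies with baseline pain, a moderator correlated with pain picks up part of that variation, and the interpretation rule credits it to the moderator. Aim 2 is meant to guide patient-treatment matching, so the label matters.
- **The control-arm clause.** If someone tests the usual-care slope by itself, regression to the mean may create or hide an association there.

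**Working it through.** The protocol gives no sample size or power figure for hypothesis 2, so there is none to reproduce. From the Statistical power section I take only the arm size, 68 completers. Two inputs are not in the document and are assumed: ρ, the correlation of pre- with post-treatment pain (0.4 to 0.7), and r, the correlation of catastrophizing with pre-treatment pain (0.3 to 0.5). The simulations used 68 per arm, an SD of change of 1, and all three moderators with their treatment interactions, with 2,000 runs per scenario.

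**1. Precision.** With equal pre and post variance σ², the change score has variance 2σ²(1−ρ). After adjustment for baseline the residual is σ²(1−ρ²). The ratio is (1+ρ)/2, so omission multiplies the standard error by √(2/(1+ρ)) and is equivalent to needing 2/(1+ρ) times the patients.

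| ρ | Variance ratio | SE inflation | Extra patients |
|---|---|---|---|
| 0.4 | 0.70 | 20% | 43% |
| 0.5 | 0.75 | 15% | 33% |
| 0.6 | 0.80 | 12% | 25% |
| 0.7 | 0.85 | 8.5% | 18% |

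In the simulation at r = 0.3, adding baseline pain cut the standard error of the CBT-by-catastrophizing interaction from 0.200 to 0.175 (ρ = 0.5) and from 0.200 to 0.186 (ρ = 0.7). Over the whole grid, omission inflated it by 6–18%. This is a little below the formula, because the moderators already carry some of the baseline-pain information. For an assumed interaction of 0.4 points per SD, power rose from 53% to 64% (ρ = 0.5) and from 50% to 58% (ρ = 0.7).

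**2. Validity of the declared test.** Write the slope of change on the moderator in an arm as its true slope plus an artefact c. Randomization makes c the same in each arm, so it drops out of the difference between slopes, which is the interaction. With no true effect, the simulated interaction estimates were about 0 and were significant in about 5% of trials, with or without baseline pain.

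**3. Usual-care slope.** Take response as the reduction, pre minus post, with no true effect. Slopes are in pain SDs per SD of catastrophizing; at ρ = 0.5 the pain SD equals the SD of change.

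- *Catastrophizing tracks the observed baseline score* and predicts later pain only through it. The unadjusted slope is r(1−ρ). At ρ = 0.5 and r = 0.3 this is 0.3 × 0.5 = 0.15 (simulated 0.154, significant in 19% of trials). With adjustment it is about 0 (significant in 4%). Over the grid the unadjusted slope is significant in 13–51% of trials.
- *Catastrophizing tracks stable pain*, not the transient part of the baseline score. The unadjusted slope is 0 (significant in 5%). The adjusted slope is −r(1−ρ)/(1−r²) = −0.15/0.91 = −0.165 (simulated −0.165, significant in 28%).

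Eligibility requires "average pain intensity in the past week of at least moderate severity (defined as ≥ 3 on the 0–10 numerical rating scale (NRS"). With a lower cut-off on baseline pain in the simulation (ρ = 0.5, r = 0.3), the unadjusted slope became 0.079 under the first mechanism and −0.080 under the second. The interaction SE inflation fell to 7% and 9% respectively.

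**4. Attribution.** Suppose the treatment effect grows by 0.3 points per SD of baseline pain and catastrophizing has no moderating effect, with r = 0.4. The expected catastrophizing interaction is 0.4 × 0.3 = 0.12. The simulation gave 0.127 without baseline pain and 0.133 with baseline pain as a main effect only. A main effect therefore does not separate the two. Only a baseline-pain-by-treatment term does.

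**The case against.** The article condenses a fuller plan. Its description of this model is four sentences long and does not list even a treatment main effect, so it is not an exhaustive list of terms, and the covariate may be in an analysis plan that is not shown. That stands as a caution. But the preceding subsection does name the covariate for hypothesis 1, and an analyst who followed the text as written would leave it out here.

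A reader might infer more: that regression to the mean will make catastrophizing look like a moderator, or that it will refute the control-arm clause of 2a. The document does not support this. It declares the interaction terms as the test, and there the artefact cancels. It sets no separate test or decision rule for the usual-care slope. The false slope also needs the moderator to track the observed baseline score. If it tracks stable pain, adjustment creates an artefact of opposite sign. So adjustment cannot be presented as the cure for that slope.

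One may also say that a marginal moderator is a legitimate target for patient matching, and that baseline pain is already an exploratory moderator. Both are fair. They are reasons to keep the baseline-pain-by-treatment term as a sensitivity analysis, not reasons to leave out the main effect.

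**Conclusion.** The point holds as a matter of precision, consistency and interpretation for Aim 2. As written, the model omits a covariate that the protocol uses for the same response in hypothesis 1 and in the stratification. The cost is an interaction standard error about 8–20% larger for ρ from 0.4 to 0.7. It is somewhat less where the moderators share information with baseline pain or where the entry threshold narrows its range. These figures rest on assumed correlations and on equal pre and post variances.

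The interaction tests are not biased by regression to the mean, and the primary hypothesis 1 test is unaffected. What remains open is attribution: a significant moderator interaction could partly reflect effect variation by baseline pain, and the model as described cannot tell the two apart.

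The control-arm clause of 2a and 2b is best judged from the contrasts between each active arm's slope and the usual-care slope. These contrasts do not prove that the usual-care slope is zero, but a stand-alone test of that slope could mislead with or without adjustment.

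**What to change.** - Add pre-treatment average pain intensity to the hypothesis 2a–2c regression, matching the hypothesis 1 model, and add sex as the other stratification factor.
- As a sensitivity analysis, add baseline-pain-by-treatment terms and report whether each moderator interaction holds over and above baseline pain.
- State that the control-arm clause of 2a and 2b is assessed by the active-versus-usual-care interaction contrasts. Report the usual-care slope descriptively only.

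The cost is two covariates in the main model, one further set of interaction terms in the sensitivity analysis and a sentence on interpretation. The data are already in the assessment schedule, and the sample size does not change.

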### Dissemination policy

The study results will be disseminated through several channels, including scientific presentations at national and international conferences and peer-reviewed scientific journal articles. Study results will also be posted on ClinicalTrials.gov under identifier NCT03782246. We will send all study participants an electronic newsletter summarizing the study findings and implications, and a link to the posted results on ClinicalTrials.gov. Results will also be posted to our laboratory website and through our UW social media accounts. The National MS Society will disseminate our study findings to MS providers, scientists, and the public through their website, newsletters, research updates, and social media accounts. Investigators will adhere to the International Committee of Medical Journal Editors guidelines for determining authorship of all presentations and publications. We do not intend to use professional writers.

## Discussion

This study was designed to address several critical gaps in the management of chronic pain. It is the first RCT to evaluate the efficacy of MBCT relative to CBT and usual care for chronic pain, which has not been done in MS nor in any other chronic pain condition. MBCT is a promising, innovative treatment that may benefit those individuals with MS who do not respond to CBT. MBCT integrates mindfulness meditation practices within a CBT-oriented framework to address not only unhelpful cognitions and behaviors but also other components central to effective pain management, such as attentional control, decoupling of attention from emotion, mindful cognitions, and meditative behavior, all of which are hypothesized to be influenced by MBCT [42]. Study findings will provide critical information about the relative benefits of both MBCT and CBT compared to one another and to usual care. The findings will also determine the value of both of these approaches as adjunctive pain interventions, and if results support the use of MBCT, will expand the currently available treatment options for people with MS and chronic pain.

In addition to evaluating the efficacy of MBCT and CBT relative to one another and to usual care, this study will address a key gap in our understanding of variability in treatment responses to two psychosocial pain interventions. Comparisons of pain psychosocial interventions often yield equivalent efficacy; however, within-group comparisons indicate that there are both responders and non-responders to specific treatments [43, 44]. That is, for any individual, two different treatments such as CBT and MBCT may not necessarily be similarly efficacious. There is an urgent need to understand those factors underlying this individual-level variability in responses across different psychosocial treatment interventions. This understanding will inform for whom different psychosocial pain interventions work. Such knowledge will lead to more precisely targeted patient-treatment matching and, ultimately, better treatment outcomes for chronic pain in MS. The present study aims to address this gap by examining pain treatment moderators of both CBT and MBCT. Moreover, this is one of the first studies to test the moderators of psychosocial treatments on the basis of an a priori theoretical framework - the LA&E model. This is important as Kazdin [45, 46] has described how the lack of theory guiding prior tests of moderation is likely a critical reason underlying why the psychotherapy field has failed to advance the development of patient-treatment-matching algorithms.

Psychosocial interventions are underutilized for addressing chronic pain, both in the general population and in people with MS, with one driver of this underutilization being limited access to such treatments [43, 47, 48]. People with chronic pain co-occurring with MS are particularly likely to have poor access to nonpharmacologic pain care [49]. To overcome this barrier, the proposed study capitalizes on an emerging delivery innovation in the form of web-based, group-delivered videoconferencing technology. The current standard delivery format for psychosocial pain interventions is in person, limiting access to only a subset of clinical settings and patients, typically those residing in urban locations. Leveraging available technology and delivering interventions in formats with broader reach affords the capacity to transcend geographical barriers and target larger, more diverse populations. Approaches such as videoconferencing also have inherent scalability potential, as it is easier to centralize and scale up such technologies for public health dissemination [50]. Remote delivery may also reduce stigma and lower the threshold for initiation of treatment, given that such technologies can be used in the privacy of one’s home and outside the mental health system. They also tend to be less expensive than traditional psychotherapies, thereby possibly making participation in such programs more viable for individuals from lower socio-economic backgrounds [50]. Although videoconferencing has increasingly been used to deliver a wide variety of healthcare interventions, rigorous RCTs of group-based videoconferencing are surprisingly absent from the literature on chronic pain. Thus, the results of this study will have important implications for overcoming access barriers and for treatment disparities in not only people with MS and pain, but also other populations experiencing pain.

As with any research design, this present study has a few potential limitations. The trial will be conducted out of a single study site, although people with a physician-verified diagnosis of MS who live anywhere in the USA will be eligible to enroll. The study sample will also be limited to individuals who have sufficient Internet access capabilities to use videoconferencing. Fortunately, Internet access and use is increasing rapidly among adults, with 92% of urban, 90% of suburban, and 78% of rural adults in the USA reporting use of the Internet in a 2018 national survey [51]. We will track and report the number of individuals interested in the study who do not have Internet access but are otherwise eligible to learn more about this limitation. This is the first clinical trial to evaluate group-based, videoconference delivery of MBCT and CBT. As such, there are no best practices or treatment guidelines to inform how to best deliver these treatments, including the experiential components of mindfulness meditation (in MBCT) and relaxation exercises (in CBT) over videoconference. Thus, there may be unanticipated challenges or problems that arise in the delivery of these treatments via videoconferencing. We will track such challenges, if they arise, as well as any technology problems that occur during the course of the study, to inform future implementation of videoconference group delivery.

In conclusion, this study seeks to expand the treatment options available to individuals with chronic pain and MS. As a group, people with MS are eager to learn nonpharmacologic strategies for managing symptoms such as pain [52]. Showing that MBCT is effective and that MBCT and CBT might be effective in different individuals has significant importance for clinical translation: this will allow for informed, a priori decisions about which treatment approach to deliver to which individual to efficiently and optimally obtain meaningful benefit for that individual*.* The study findings may also have relevance to other people experiencing chronic pain, including other people with neurologic conditions such as traumatic brain injury, where pain is common and access to evidence-based nonpharmacological treatment is limited.

